### Participants

2.2

We will include a total of 72 patients who are suffering from BCT. After the patient's accident, such as falls, kicks, fights, or traffic accidents, they will be sent to the emergency room and visit a chest surgical out-patient clinic for treatment and follow-up. Those who meet the inclusion criteria will be informed about the study and can freely choose to participate. They will sign the informed consent and will be randomized accordingly, with commencement of the study occurring immediately. The patients are allowed to drop out from the study at any time point of the study.

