### Acupuncture group (Acu)

2.10

The patient will lay down in a supine position on the treatment bed and allowed an adaptive relaxation period of 5 minutes. The acupuncturist will start to sterilize the specific body surface areas over the acupoints with a 70% alcohol pad. Accordingly, the bilateral acupoints of GB 36 (Waiqiu), GB 34 (YangLingQuan), ST 36 (Zusanli), LI 4 (HeGu), LU 7 (LieQue), TH 5 (Waiguan) were chosen for both groups. Each patient will receive 12 press tack needles in total. The needle's depth of insertion will be 0.6 mm. The acupuncturist will manually press the press tack needles over the above-mentioned acupoints without any needle manipulation or “De Qi” sensation. The participants will lay on the treatment bed for the duration of 30 minutes. After the aforementioned process, the vital signs, pain levels, and flowmeter will be recorded again to represent the immediate effect after acupuncture. Finally, the acupuncturist will educate the patients about the total number of press needles and the allotted time of retention. The press tack needle retention time will total 4 consecutive days.

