### Outcome measures

2.13

The main outcome measurement will be the pain levels of both rest and mobile status for the BCT patients (the mobile status includes cough, deep breath, and turn over on the bed). The patient will measure their pain according to 3 subjective pain scales, namely the NRS, and FRS before treatment, 30 minutes after treatment and 4 days after the press tack needles/placebo intervention. Furthermore, a follow-up will assess the NRS pain scale telephonically at 14 days and 3 months after the initial intervention.

Secondary outcome measurements will include the improvement of respiratory function, sleep quality, and amount of medication used (specifically analgesics and muscle relaxants). We used the portable triflow flowmeter and VSH sleep scale as objective tools for the aforementioned purposes. The patients will be educated on the use of the flowmeter by the affiliated thoracic surgeon. Patients will be allowed as much time as needed to practice the use of the flowmeter before the first measurement is taken. When the patient is ready, the study personnel will commence the measurements of 3 attempts, and will record the best 2 attempts. The triflow flowmeter measures the amount of air the patient can exhale; it has 3 chambers with their own balls that require air pressures from 600 to 1200 cm^3^ per second to elevate. 1200 cm^3^ is the highest score and indicates good exhalation power. The above process will be done before intervention, 30 minutes after intervention and 4 days after the intervention. The patient will also answer the VSH sleep scale in Mandarin to evaluate the sleep quality of the night before the clinic visit. They will complete the questionnaires accordingly at every clinic visit, for a total of 2 times (on day 1 and day 4). Finally, on the 4th day after the initial intervention, participants will bring back the prescribed medication, including analgesics and/or muscle relaxants that were left unused, to be measured for the amount of medication used.

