### Statistical analysis

2.19

Statistical analyses will be performed using SPSS software version 22.0 (SPSS Inc, Chicago, IL). The demographic data between Acu and Con groups including gender, age, and clinical characteristics will be compared using the Student's *t* test and Chi-squared test. Between-group values will be measured by the paired *t* test. For the multiple pain scale and sleeping quality measurements, a one-way ANOVA will be used according to the previous similar study.^[11]^ We will also implement the advanced repeat measurement analysis in the study. Data will be presented as mean ± standard deviation. A *P*-value of less than .05 will be considered statistically significant.

Subgroup analysis will be done based on the following: age, sex, number of treatments complete, number of hours of needle retention, number of rib fractures, pulmonary complications, hospitalization, number of days from patient's injury to the first treatment, Triflow score, medication use, body mass index, and ISS. In cases of small sample size, the Mann–Whitney *U* and the Wilcoxon sign rank test will be implemented accordingly. Missing data will be analyzed using the pairwise deletion method.

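### At least three of the twelve planned subgroup factors are known only after randomisation, and one of them is a secondary outcome

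*Protocol article*

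**What the plan says.** Section 2.19 (Statistical analysis) of the protocol article names the subgroup factors in one sentence. It begins with age and sex, continues "number of treatments complete, number of hours of needle retention, number of rib fractures, pulmonary complications, hospitalization", and ends "number of days from patient's injury to the first treatment, Triflow score, medication use, body mass index, and ISS". That makes twelve factors. The sentence does not limit them to baseline values and gives no measurement time for any of them.

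Other sections fix when several of these factors become known:

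- Section 2.2: consenting patients "will be randomized accordingly, with commencement of the study occurring immediately".
- Section 2.10: "The press tack needle retention time will total 4 consecutive days". Section 2.11 gives the same period for the placebo.
- Section 2.13: "on the 4th day after the initial intervention, participants will bring back the prescribed medication", so that the amount used can be measured.
- Section 2.12: the drugs are for pain relief, and patients may stop them when they choose.
- Section 2.13 also states: "Secondary outcome measurements will include the improvement of respiratory function, sleep quality, and amount of medication used". Respiratory function is measured by Triflow before, 30 minutes after and 4 days after the intervention.

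**The concern.** A subgroup comparison keeps the protection of randomisation only if subgroup membership is settled before, or cannot be influenced by, the allocated treatment. Medication use does not meet that condition here. Patients take the drugs because of pain, may stop when they wish, and the trial hypothesises (Section 1) that true needles reduce pain more than placebo. If that is so, acupuncture patients with low use are a different kind of patient from placebo patients with low use, and the difference between them is no longer the treatment effect.

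Treatments completed and retention hours measure adherence. A comparison within levels of adherence depends on why patients kept or lost their needles, and randomisation does not balance that.

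What is at stake is the interpretation of the subgroup results. The report could give effects by medication use or retention time that look like randomised evidence and are not. The main pain comparison does not depend on them.

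**Working it through.** The plan gives no figure on this point to reproduce. The check is a classification of the list, followed by an illustration of size.

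**Step 1. Classify the twelve factors by when they are known.**

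| Factor | Timing from the document |
|---|---|
| Age, sex, number of rib fractures, days from injury to first treatment, body mass index, ISS | Patient or injury features, settled at enrolment |
| Number of treatments completed | After randomisation: treatment follows allocation (2.2) |
| Hours of needle retention | After randomisation: worn for 4 days after placement (2.10, 2.11) |
| Medication use | After randomisation: returned drug counted on day 4 (2.13) |
| Pulmonary complications, hospitalisation | Not stated in 2.19 |
| Triflow score | Measured once before and twice after treatment (2.13); time point for the subgroup not stated |

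The counts are 6 baseline + 3 after randomisation + 3 without a stated time = 12. So three factors are certainly post-randomisation. The number is five if complications and hospitalisation are follow-up events, and six if Triflow is a post-treatment value.

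Follow-up is the more natural reading of complications and hospitalisation. Patients are randomised in an out-patient clinic and treated at once, and Section 2.15 mentions hospitalisation as care after an adverse event. The text does not settle it.

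**Step 2. Illustrate the size for medication use.** All values here are assumptions; the documents give none.

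- Pain: Y = (normal, SD 2) + effect × arm.
- Medication: M = b × Y + (normal, SD 1) - g × arm, where b is units of drug per NRS point and g is any direct lowering of use by the arm.
- Split at the overall median of M, then take the difference in mean Y between arms within each half, by simulation of 4 million patients.

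The within-arm correlation of pain and medication is 2b / √(4b² + 1). For b = 0.7 it is 1.4/√2.96 = 0.81; for b = 0.3 it is 0.6/√1.36 = 0.51; for b = 0.1 it is 0.2/√1.04 = 0.20.

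| True effect | b | g | Effect seen in each half |
|---|---|---|---|
| -1.0 | 0.7 | 0 | -0.58 |
| -1.0 | 0.3 | 0 | -0.83 |
| -1.0 | 0.1 | 0 | -0.98 |
| 0 | 0.7 | 0 | 0.00 |
| 0 | 0.7 | 0.7 | +0.42 |

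The effect is understated by 42%, 17% and 2% in the first three rows, by about the same amount in the high-use and low-use halves. The fourth row shows that when the arm changes neither pain nor medication there is no bias. The last row shows that a spurious effect on pain needs a further assumption, namely that the arm lowers medication use by a route other than pain.

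**The case against.** The strongest reply has four parts.

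- **Count.** A reader might infer that five or more factors are post-randomisation. The document does not establish that. Patients come through the emergency room and may enter up to a week after injury (2.2, 2.3), and lung contusion is named among the injuries of blunt chest trauma (Section 1). Complications and hospitalisation could therefore describe status at enrolment. This part stands: three is certain and five is probable.
- **Certainty of bias.** A reader might infer that all these subgroup effects will be biased. Bias arises only where treatment affects the factor. The devices look identical and are worn at the same points for the same period, and nothing in the document shows that retention or completion would differ by arm. This part stands too. For medication use, however, bias is the expected result if the trial's hypothesis is true.
- **Number of tests.** A reader might go further and object to twelve factors tested at P < .05 without an interaction test. Two levels each would give 24 tests and 1 - 0.95^24 = 0.71. The document does not support this as a finding. Section 2.19 does not say how subgroups are tested, its small-sample sentence is not tied to them, and a condensed article may leave such detail to the analysis plan. The 0.71 also needs independent tests, whereas all splits reuse the same patients; a simulation re-splitting 56 patients gave about 49%.
- **Weight.** These are secondary analyses, and nothing bases the trial's conclusion on them. This is true and limits the severity.

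None of this removes the core point. The list of factors is a stated choice, and three of its entries are adherence or outcome measures.

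**Conclusion.** The concern holds in a limited form. Section 2.19 commits to subgroups by treatments completed, hours of needle retention and medication use, all known only after randomisation, and medication use is itself a secondary outcome. Comparisons within those subgroups are not protected by randomisation and can be biased; for medication use this is expected under the trial's own hypothesis. Pulmonary complications, hospitalisation and Triflow need a stated time point before they can be judged.

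The size cannot be computed from the document. On the assumptions shown, a true -1.0 shrinks to between -0.58 and -0.98, and a spurious +0.42 arises only if the arm also acts on medication use directly. Because the shrinkage is alike in both halves, the illustration does not show a false contrast between high and low users. The randomised comparison of pain is untouched. The point should be corrected, but it does not threaten the trial's main result.

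**What to change.** Reword the subgroup sentence in Section 2.19 as follows.

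- Restrict subgroup analysis to factors fixed before randomisation: age, sex, number of rib fractures, days from injury to first treatment, body mass index, ISS, and Triflow at its pre-intervention value only.
- Report treatments completed and hours of needle retention by arm, as adherence.
- Report medication use as an outcome by randomised arm, as Section 2.13 already intends.
- Report pulmonary complications and hospitalisation as outcomes by arm, unless they are defined as present at enrolment. If that is what is meant, say so.

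The number of treatments completed also cannot be interpreted until the Abstract, which gives a single treatment, and Section 2.8, which gives two, are reconciled.

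The cost is one paragraph of wording and the loss of a few exploratory analyses. Design, sample size and data collection do not change.

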### Randomization and allocation concealment

2.6

The participants will be randomized into 2 groups with a 1:1 ratio produced by the SPSS program software, version 22. A computer-based simple random sampling with a 1:1 ratio without stratification will be used. A number (1–72) will be affiliated to each patient at the time of their first visit to the out-patient clinic and after completing the informed consent. The number, patient name, and date of birth will be written down on a non-transparent envelope by a study nurse 1 (researcher [name]). Inside the envelopes, there will be 14 separate sterile press tack needles or identical looking press tack placebos. The envelopes in both groups will appear identical. Study nurse 1 will write down the number, patient name, and intervention in an electronic chart and create a file for each patient.

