### Drug treatment

2.12

Both groups of participates will also receive the prescribed analgeasic medication and/or muscle relaxants. The frequency of the prescribed medicine is 3 to 4 times a day along with meals and before sleep for 7 days. The purpose of the medication is for pain relief, therefore, the participants can discontinue the medication at will.

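### At least three of the twelve planned subgroup factors arise after randomisation, so Acu-versus-Con comparisons within them are not randomised comparisons

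*Protocol article*

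**What the plan says.** Section 2.19 says that subgroup analysis will be done on twelve factors: age, sex, "number of treatments complete, number of hours of needle retention, number of rib fractures, pulmonary complications, hospitalization", and then "number of days from patient's injury to the first treatment, Triflow score, medication use, body mass index, and ISS". It gives no time of measurement for any of them and sets no rule that only baseline values count.

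Other sections place some of these factors in time:

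- **Start of treatment.** The Participants section says that consenting patients "will be randomized accordingly, with commencement of the study occurring immediately".
- **Secondary outcomes.** Outcome measures states: "Secondary outcome measurements will include the improvement of respiratory function, sleep quality, and amount of medication used". Medication use is counted on day 4 from the drugs brought back. Triflow, the respiratory tool, is read once before the intervention and twice after it (30 minutes and 4 days).
- **Analgesics and muscle relaxants.** Drug treatment says that these are for pain relief and that "the participants can discontinue the medication at will".
- **Retention.** Procedure/interventions and the two arm descriptions set a wearing time of 4 days from application.

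**The concern.** A subgroup comparison keeps the protection of randomisation only if membership of the subgroup is settled before allocation, or at least cannot be changed by it. Several listed factors describe what happened to the patient afterwards. If the needle relieves pain, patients in the Acu group may take fewer tablets. A high-use Acu patient and a high-use Con patient are then no longer alike apart from treatment, because they reached that stratum by different routes. Testing the interaction in place of separate within-stratum tests does not help, since the stratifying variable itself has been affected by allocation.

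At stake is the reading of the subgroup tables. A real effect may look smaller at every level of medication use than it is overall, and under some conditions an effect may appear that does not exist.

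**Working it through.** **Step 1. Sort the twelve factors by time.** Randomisation is at the first out-patient visit, and treatment follows at once.

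| Factor | Status in the article |
|---|---|
| Age, sex, rib fractures, days from injury to first treatment, body mass index, ISS (6) | Fixed at entry. A further chest film is taken on day 4, so the fracture count should be tied to the entry film |
| Treatments complete, retention hours, medication use (3) | After allocation |
| Triflow score (1) | One reading before and two after; 2.19 does not say which is used |
| Pulmonary complications, hospitalization (2) | No time given |

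6 + 3 + 1 + 2 = 12. The certain count is three. It reaches six only if all the factors without a stated time are post-allocation values.

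On the last row the article points both ways. Patients enter from an out-patient clinic, and the Adverse events section mentions hospitalization as care after an event and pneumothorax as a possible event. But patients pass through the emergency room first, may enter up to a week after injury, and the Introduction describes lung contusion and hospital admission as features of chest trauma itself.

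**Step 2. Size of the distortion for medication use.** The article has no figure to reproduce here, so the inputs are assumptions. Pain Y has SD 1 within each arm, and its mean is lower by b in Acu. Medication use is M = rY + √(1 − r²)·e, with e independent standard normal noise, so use follows pain with within-arm correlation r. Patients are split at the pooled median of M, which lies at −rb/2.

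With λ(x) = φ(x)/(1 − Φ(x)), the Acu − Con difference in the upper half is

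−b + r[λ(rb/2) − λ(−rb/2)] ≈ −b(1 − 2r²/π),

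and by symmetry it is the same in the lower half.

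For b = 0.50:

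- r = 0.3: 0.50 × (1 − 0.637 × 0.09) = 0.50 × 0.943 = 0.47
- r = 0.5: 0.50 × (1 − 0.637 × 0.25) = 0.50 × 0.841 = 0.42
- r = 0.7: 0.50 × (1 − 0.637 × 0.49) = 0.50 × 0.688 = 0.34

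Simulation with 2,000,000 patients gave 0.47, 0.42 and 0.34. With the effect size used in the article's Sample size calculation (1.124365), the values for r = 0.5 and 0.7 are 1.124365 × 0.841 = 0.95 and 1.124365 × 0.688 = 0.77.

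**Step 3. When there is no distortion.** If allocation does not shift medication use, the simulated within-half difference under no pain effect is zero to within 0.002 SD. The bias therefore needs the treatment to act on the factor.

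**Step 4. Compare with sampling error.** With 36 per arm, a median split leaves about 18 per arm in each half. The standard error of a difference is then about √(2/18) = 0.33 SD. The loss in step 2 for r = 0.5 to 0.7 is 0.50 − 0.42 = 0.08 to 0.50 − 0.34 = 0.16 SD, which is under half a standard error.

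**The case against.** The strongest reply is that these are secondary tables. Section 2.19 gives them no confirmatory role, the main pain comparison does not depend on them, and step 4 shows that noise would exceed the bias in a trial of 72. All of this stands, and it limits the weight of the point. It does not make the tables sound. They are not labelled exploratory, one P < .05 rule covers every analysis, and a bias is not made acceptable by being small beside the sampling error.

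A reader might go further in three ways that the article does not support.

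- **That five or six factors are certainly post-randomisation.** No recording time is given for pulmonary complications or hospitalization, and either could date from the injury. Triflow has a valid reading before the intervention.
- **That a useless needle will look beneficial among patients who kept it in for 4 days.** Simulations can produce this (a false benefit of 0.18 to 0.32 SD). They assume that 20 to 40% of Acu patients remove tacks early for pain-related reasons (correlation 0.5) while removal in Con is random. Nothing in the article states that asymmetry: the devices look identical, patients are blinded, and the tack is 0.6 mm long. If removal followed the same process in both arms, the bias under no effect would be zero.
- **That stratifying by medication use will show a false harm.** This needs the needle to cut drug use while leaving pain unchanged. With a drop of 0.5 to 1 SD and correlation 0.3 to 0.7, the simulated false harm is 0.09 to 0.44 SD. If drug use simply follows pain, a needle without effect on pain does not shift it.

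It is also fair to say that treatments complete may hardly vary. The Abstract gives one treatment per patient and Procedure/interventions gives two.

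**Conclusion.** The point holds for three factors: treatments complete, retention hours and medication use. For Triflow score, pulmonary complications and hospitalization, the fault is that 2.19 does not restrict them to values before allocation. The principle rests on the article's own timing and needs no assumed number. The size does: a shrinkage from 0.50 to about 0.42 to 0.34 SD rests on the assumed correlation of 0.5 to 0.7 and on medication use following pain. Larger distortions, or effects created from nothing, need further assumptions that the article neither states nor rules out. A reader might infer that the trial's main result is compromised. It is not, because the overall comparison of pain between the randomised groups does not condition on any of these factors. The plan should be corrected, but the fault is confined to the subgroup analyses.

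**What to change.** In section 2.19:

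1. Limit subgroup factors to values fixed before allocation: age, sex, rib fractures on the entry film, days from injury to first treatment, body mass index, ISS, and Triflow score named as the pre-intervention reading. Keep pulmonary complications or hospitalization only if present before randomisation, and say so.
2. Remove treatments complete, retention hours and medication use as subgroup factors.
3. Describe treatments received and retention hours by arm. Keep medication use as the secondary outcome that it already is. Report by arm any pulmonary complications and hospitalization arising after allocation.

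Separately, reconcile the Abstract and Procedure/interventions on the number of treatments.

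The change needs no additional patients. It costs a few exploratory tables that could not be read as treatment effects. A complier-type estimate of the effect of full wear would be optional at most: it needs a definition of compliance and further assumptions, and would be very imprecise with 72 patients.

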### Follow-up

2.14

After the initial visit to the chest surgical out-patient clinic, the participates in both the Acu and Con groups will be expected to return 4 days after acupuncture/placebo treatments for needles/placebos withdrawal along with chest plain film, NRS, FRS scores, flowmeter, respiratory function, VSH sleep scale assessments, and amount of medication used. On the 14th day and at 3 months after the initial intervention, a study personal will arrange a telephonic consultation to enquire about the pain scale (NRS) and any adverse effect related to the acupuncture treatment and the chest trauma (Fig. 4).

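### Subgrouping by medication use splits patients on a day-4 outcome that the needles can change, so the within-level needle effect is biased if the needles work

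*Protocol article*

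**What the plan says.** Section 2.19 of the protocol article introduces a list of twelve factors with "Subgroup analysis will be done based on the following". The list ends "Triflow score, medication use, body mass index, and ISS". Nothing limits medication use to a value fixed before randomisation.

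Three other sections define what medication use can be:

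- **Drug treatment (2.12).** Both arms are prescribed analgesics and/or muscle relaxants for 7 days, and "The purpose of the medication is for pain relief, therefore, the participants can discontinue the medication at will".
- **Outcome measures (2.13).** A secondary outcome is the "amount of medication used (specifically analgesics and muscle relaxants"). For its measurement, "on the 4th day after the initial intervention, participants will bring back the prescribed medication", including the drugs "that were left unused, to be measured for the amount of medication used".
- **Follow-up (2.14).** The day-4 visit collects "NRS, FRS scores, flowmeter, respiratory function, VSH sleep scale assessments, and amount of medication used", so the drug count and the day-4 pain ratings come from the same visit.

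Section 2.2 has patients randomised after consent and started at once. No measure of drug use before enrolment is described.

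**The concern.** A subgroup factor should be something that treatment cannot alter. Randomisation then still balances the arms within each level. Medication use by day 4 does not meet that condition. The protocol itself treats it as a possible effect of treatment by making it an efficacy outcome. It also links use to pain, since the drugs are for pain relief and may be dropped freely.

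Suppose the needles work. Some Acu patients who would otherwise have kept taking tablets stop them. The Acu stoppers then include people with worse underlying pain than the Con stoppers. The Acu patients who continue despite the needles are also a worse group than the Con continuers. Within either level, the comparison sets needles in harder cases against placebo in easier ones.

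A reader of the published table would take it as showing whether light or heavy drug users benefit more, and it cannot show that. With few patients per level, it could suggest no benefit in one level from selection and low power alone.

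**Working it through.** **The plan's own figure.** Section 2.16 gives 18 per group at 95% power with d = 1.124365. An independent two-sample t test at one-sided alpha 0.05 reproduces this (power 0.952 at n = 18); two-sided alpha would need 22. That effect size is for pain immediately after treatment. The protocol gives no day-4 effect, drug effect or stopping rate, so the size of this problem has to rest on assumptions.

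**Inputs**

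- Patients: 36 per arm less 20% dropout = 28.8, taken as 29 (section 2.16).
- Assumed needle effect at fixed drug use: 0.75 SD, which gives 80% power at 29 per arm with two-sided alpha 0.05 (exact value 0.749).
- Assumed: half of Con stop the drugs by day 4.
- Assumed drug effect in those still taking it: 0.25 to 1.0 SD.
- Assumed link of stopping to pain: noise SD s from 0.5 (tight) to 3 (loose).

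**Model.** Pain at fixed drug use is U ~ N(μ, 1), with μ = 0 in Con and −0.75 in Acu. A patient stops if U + noise < 0. Observed pain is U, less the drug effect if the patient continues. With r = 1/√(1 + s²):

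- P(stop) = Φ(−μr)
- mean U in stoppers = μ − r·φ(μr)/Φ(−μr)
- mean U in continuers = μ + r·φ(μr)/Φ(μr)

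The drug effect is constant within a level, so it cancels from the within-level comparison.

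**Worked case, s = 1** (r = 0.7071)

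- Acu stop rate: Φ(0.530) = 0.702.
- Stoppers: Con mean −0.7071 × 0.3989/0.5 = −0.5642; Acu mean −0.75 − 0.7071 × 0.3466/0.702 = −1.0991. Difference 0.5349.
- Continuers: Con mean 0.5642; Acu mean −0.75 + 0.7071 × 0.3466/0.298 = 0.0726. Difference 0.4916.

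**All cases** (SD units; the true effect at fixed drug use is 0.75; the gap is 0.75 minus the within-level difference, that is, how much worse needle-free pain is in Acu)

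| s | Acu stop | Difference, stoppers | Difference, continuers | Gap, stoppers | Gap, continuers |
|---|---|---|---|---|---|
| 0.5 | 75% | 0.42 | 0.33 | 0.33 | 0.42 |
| 1 | 70% | 0.53 | 0.49 | 0.22 | 0.26 |
| 2 | 63% | 0.66 | 0.65 | 0.09 | 0.10 |
| 3 | 59% | 0.70 | 0.70 | 0.05 | 0.05 |

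Standardised within level, the differences are about 0.55 to 0.73 in stoppers and 0.49 to 0.72 in continuers, roughly 3% to 35% below 0.75. With the needle effect set to 0, every within-level difference is 0.

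**Against the overall day-4 difference.** Overall difference = 0.75 − drug effect × (Acu stop rate − 0.50).

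- Lowest: continuers, s = 0.5, drug 0.25. Overall 0.75 − 0.25 × 0.249 = 0.688; 0.329 − 0.688 = −0.36.
- Highest: stoppers, s = 3, drug 1.0. Overall 0.75 − 1.0 × 0.094 = 0.656; 0.704 − 0.656 = +0.05.

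The direction relative to the overall result is therefore not fixed.

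**Numbers per level.** Con splits into 14 or 15 in each level. Acu has 29 × 0.59 to 0.75 = 17 to 22 stoppers (power about 35% to 51%) and 7 to 12 continuers (power about 18% to 43%).

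**A second model.** Here drug use is an amount, split at its median: use = U − g × (Acu) + N(0, 1), with needle effect t on pain. Negative differences favour Acu.

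- t = 0.50, g = 0.5: overall −0.50, within levels −0.34 (32% smaller).
- t = 1.124, g = 1.0: within levels −0.81 (28% smaller).
- t = 0, g = 0.5: within levels +0.16, a false harm.
- t = 0.50, g = 0: within levels −0.50, no bias.
- t = 0.50, g = 0.5, drug relief 0.2 per unit of use: overall −0.40, within levels −0.30.

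Both models agree that bias needs the needles to change drug use and pain to drive it.

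**The case against.** The strongest objection is that the point is too narrow. The same list holds the number of treatments completed and the hours of needle retention, which can only be known after randomisation. Pulmonary complications and hospitalisation may also arise after it. Removing medication use alone leaves those in place. This is right and widens the remedy, but it does not weaken the point. Medication use is the clearest case because the protocol also declares it an outcome. Triflow score differs, because it has a pre-treatment value that could be used safely.

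Second, the factor has no stated time point or cut-off, and a condensed article may leave that to the full protocol. A grouping by type of drug prescribed is conceivable. But nothing in the text says so, and the only medication measure described is the amount used by day 4.

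Third, every input to the size is assumed, and the stop/continue split simplifies a measured amount. That stands. If stopping follows pain only loosely, the bias is about 0.05 SD, negligible beside sampling error in groups this small.

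Fourth, the trial exists because efficacy is unknown, so bias is conditional. This also stands. The condition is that the needles change pain or drug use, which is what the trial hypothesises.

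**Conclusion.** The concern holds. As written, section 2.19 splits patients on a post-randomisation efficacy outcome, and the within-level comparison does not estimate the needle effect among lighter or heavier drug users. Under the main model's assumptions it understates the effect at fixed drug use in both levels, by 0.05 to 0.42 SD out of 0.75. The mechanism follows from the protocol's own text; the size is illustrative only.

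The consequence is limited. The comparison of all randomised patients is unchanged by this subgroup, and no confirmatory claim is attached to it. At-will stopping is not itself a serious problem: in the same model it lowers the overall standardised day-4 effect by only 1% to 13% (power 69% to about 80%), and the 30-minute rating is little affected. This is a point to consider, not one that threatens the trial.

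**What to change.** Delete medication use from the subgroup list in section 2.19. Keep it as the planned secondary outcome, compared between arms in all randomised patients with data, and report it beside day-4 NRS. Equal pain with lower use would support an analgesic effect; lower pain with higher use should not be read as clear analgesia. A rank analysis combining pain and drug use is optional.

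If a medication subgroup is wanted, use a factor fixed before randomisation. One example is the class prescribed (analgesic alone or with a muscle relaxant), provided it is recorded before the patient number is assigned.

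Apply the same test to the rest of the list. Drop treatments completed and hours of retention as subgroup factors, limit pulmonary complications and hospitalisation to events before randomisation, and specify the pre-treatment Triflow score.

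The medication rule and the main outcome stay as they are. For medication use, the change is one item removed from a list of twelve, with no new visits or tests; a substitute factor needs only the prescription noted before allocation. What is lost is one exploratory subgroup, and pain and drug use must be read side by side instead of in one table.
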